### Grading of retinal imaging and outcomes to be measured

Multimodal imaging of the participants in the enhanced protocol will be graded monthly by research fellows according to Table 3.

**Table 3 pone.0355953.t003:** Detailed description of grading in the enhanced protocol.

Modality	Feature	Criteria
Ultrawide Field Fundus Photography	Drusen	The biggest drusen size within the 2-disc diameters of fovea • Small (≤63 µm) • Medium (>63 µm and ≤125 µm) • Large (>125 µm)
	AMD pigmentary abnormalities	Any definite hyper- or hypopigmentary abnormalities
	Hemorrhage^*^	Blood
	Fibrosis^*^	Obvious white or yellow mounds of fibrous-appearing tissue that were well defined in shape and appeared solid
	Atrophy^*^	Partial or complete depigmentation patches ≥175 μm in longest linear dimension that had ≥ 1 of these additional characteristics: sharply demarcated borders, visibility of underlying choroidal vessels, excavated or punched out appearance on stereoscopy of CFP
FAF		Atrophy:Hypoautofluorescent (black level similar to optic nerve head or retinal blood vessels) area with sharply demarcated borders FAF will also be used for confirming the presence of subretinal drusenoid deposits (areas of hyperfluorescent on the centre and surrounded by a Hyporeflective halo, forming a target appearance)
OCT	Central Subfield Thickness (CST)	The average thickness of the retina within the central 1-mm ETDRS subfield.
	Subfoveal choroidal thickness (SFCT)	The distance between the Bruch membrane and inner scleral surface measured in µm on the central B-scan using the caliper tool in the Heidelberg Spectralis platform.
	Drusen	• Soft drusen: focal thickening between the RPE and BM, ≥ 100μm diameter • Hard drusen: focal thickening between the RPE and BM, < 100μm diameter • Subretinal drusenoid deposits (SDD): mounds or cone-shaped structures with medium to high reflectivity, located either at the ellipsoid zone or between the ellipsoid zone and the RPE surface • Cuticular Drusen: blunted triangular elevations in a sawtooth configuration • Hyporeflective drusen core (HDC): drusen that have Hyporeflective space within them, with a minimum height of 40 μm • Pachydrusen: drusen located adjacent to pachyvessels
	Pigment epithelial detachment (PED)	>100μm separation of RPE and BM, • Serous PED: optically clear or hypo-reflective sub-RPE elevation • Drusenoid PED: dome-shaped RPE elevation with more homogeneous internal reflectivity, consistent with drusenoid material • Fibrovascular PED: irregular RPE elevation with heterogenous internal reflectivity
	Double layer sign (DLS)	a shallow irregular RPE elevation with separation between the RPE and Bruch’s membrane <100μm • Thin DLS: the space between RPE and Bruch’s membrane is occupied by a single zone of low-to-moderate reflectivity • Thick DLS: the space between RPE and Bruch’s membrane is occupied by at least two distinct zones with varying reflectivity Shallow irregular RPE elevation (SIRE): ≤ 100μm separation BM to RPE (height), ≥ 1000μm length of shallow continuous detachment, subset of DLS
	Intraretinal fluid (IRF) ^*^	Accumulation of the fluid in the retina, with formation of cystoid spaces.
	Subretinal fluid (SRF) ^*^	Accumulation of the fluid under the retina. Separation of the neurosensory retina from the RPE by fluid.
	Acquired vitelliform lesions (AVL)	Hyperreflective material between the RPE and photoreceptor layer, often appearing as a dome-shaped elevation with homogeneous hyperreflectivity of the subretinal deposit, although they may appear hyporeflective in some areas, particularly in the superior portions of the lesion.
	Hyperreflective material (HRM) ^*^	Exudation material that is hyperreflective, • subretinal, • sub-RPE space, • both-if RPE is not detectable HRM boundary • well-defined • ill-defined
	Intraretinal hyperreflective foci (HRF)	Hyperreflective lesions located within the neurosensory retinal layers (i.e., above the RPE band and exhibiting reflectivity comparable to that of the RPE band
	Irregular RPE	Nonspecific RPE changes, including molting of RPE, RPE thickening, hyperreflective spike of RPE et al.
	Choroidal hypertransmission	Increased signal transmission into the choroid beneath an area of RPE attenuation or loss
	Atrophy	including cRORA, iRORA (Incomplete RPE and outer retinal atrophy), cORA (Complete outer retinal atrophy), iORA (Incomplete outer retinal atrophy)
	Incomplete RPE and outer retinal atrophy (iRORA)	discontinuous signal hypertransmission into the choroid with attenuation or disruption of the RPE, and overlying photoreceptor degeneration
	Complete RPE and outer retinal atrophy (cRORA)	(1) a region of hypertransmission of at least 250 µm in diameter, (2) a zone of attenuation or disruption of the RPE of at least 250 µm in diameter, (3) evidence of overlying photoreceptor degeneration, and (4) absence of scrolled RPE or other signs of an RPE tear
OCTA		• Choroidal vascularity index (CVI) • Choriocapillaris flow area Those variables will be measured by the DREAM OCT in-built software and the average values at Early treatment diabetic retinopathy study (ETDRS) 0–1, 0–3, 0–6 mm areas will be documented. Abnormal flow signal in the outer retina/sub-RPE space or neovascular network visible on en-face view of those slabs

* These variables will be graded just in late AMD stage

The primary study outcome will be progression to late AMD, defined as 1- neovascular AMD (the development of macular neovascularization (MNV)) and/or 2- Geographic atrophy (GA, defined as atrophy lesions seen on CFP and FAF and further confirmed by the presence of complete retinal pigment epithelium and outer retinal atrophy (cRORA) on OCT, in the absence of present or previous MNV), during follow-up.

The rate of progression to late AMD will be reported, with event time assigned to the first visit at which GA or MNV is detected. The rate and time to event of progression from non-exudative neovascular AMD, detectable abnormal flow signal in the outer retina/sub-RPE space on OCTA and no exudative sign or macular fluid on OCT imaging, to exudative neovascular AMD will also be reported.

The prevalence of each multimodal imaging biomarkers alongside the rate of quantitative biomarkers and their longitudinal changes will be reported. By integrating those biomarkers with clinical (medical, drug and social history), genetic, and metabolomic data, we will assess their relative risk for progression and will present potential predictors. Furthermore, the identified prognostic factors may be used to explore clinically meaningful risk strata and inform the development of an AMD staging framework tailored to the Asian population. Using that classification, the rate of progression to different stages of AMD through years of follow-up will be reported.

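### Table 3 defines iRORA by pattern and cRORA by size, so some atrophic lesions get neither grade and others get both

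*Protocol article*

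**What the plan says.** The section on grading of retinal imaging and outcomes has research fellows grade the enhanced-protocol images by Table 3. The OCT rows that matter here are these:

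- **Atrophy** is an umbrella row, "including cRORA, iRORA (Incomplete RPE and outer retinal atrophy), cORA (Complete outer retinal atrophy), iORA (Incomplete outer retinal atrophy". cORA and iORA are named there but not defined further.
- **iRORA** is "discontinuous signal hypertransmission into the choroid with attenuation or disruption of the RPE, and overlying photoreceptor degeneration". No size is given.
- **cRORA** has four criteria: "a region of hypertransmission of at least 250" µm in diameter, "a zone of attenuation or disruption of the RPE of at least 250" µm in diameter, photoreceptor degeneration above it, and "absence of scrolled RPE or other signs of an RPE tear". Continuity of the signal is not mentioned.
- **Choroidal hypertransmission** has its own row: "Increased signal transmission into the choroid beneath an area of RPE attenuation or loss". It has no size or pattern limit, and no asterisk restricting it to late AMD.
- **Irregular RPE** is also separate: "Nonspecific RPE changes, including molting of RPE, RPE thickening, hyperreflective spike of RPE et al".

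Geographic atrophy, one of the two components of the primary outcome, is "atrophy lesions seen on CFP and FAF and further confirmed by the presence of complete retinal pigment epithelium" and outer retinal atrophy on OCT, without present or past MNV. The same section promises the prevalence and longitudinal change of each imaging biomarker, their relative risk for progression, and possible use in an Asian staging framework.

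**The concern.** The names incomplete and complete suggest two steps on one scale, but the two rows use different scales. Take a lesion 180 µm wide with RPE disruption and photoreceptor loss. If its signal is patchy it is iRORA. If its signal is solid it is not iRORA, because the signal is continuous, and not cRORA, because it is too small. The more solid lesion therefore receives the lower grade. At the other end, a large lesion with patchy signal satisfies both rows.

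iRORA has its own row, so it is one of the biomarkers to be reported. Natural history and imaging predictors are the study's specific aim, and an Asian image classification is a secondary aim (Study setting). A grade that omits some lesions and shares others with the next grade is a poor basis for either. If graders follow the text, solid small lesions sit in the iRORA-negative group. If some graders follow the text and others the evident intent, the same lesion is labelled differently between graders or visits.

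**Working it through.** The plan gives no figure to reproduce. The check is a cross-classification of the two definitions.

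**Inputs (Table 3).** iRORA requires discontinuous hypertransmission, an RPE defect and photoreceptor degeneration. cRORA requires hypertransmission of at least 250 µm, an RPE defect of at least 250 µm, photoreceptor degeneration and no tear. Throughout, an RPE defect and photoreceptor degeneration are taken as present and a tear as absent.

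**Combinations.** 2 patterns × 2 hypertransmission sizes × 2 RPE-defect sizes = 8.

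| Pattern | Hypertransmission | RPE defect | Grade as written | Grade after the fix |
|---|---|---|---|---|
| Continuous | <250 µm | <250 µm | neither | iRORA |
| Continuous | <250 µm | ≥250 µm | neither | iRORA |
| Continuous | ≥250 µm | <250 µm | neither | iRORA |
| Continuous | ≥250 µm | ≥250 µm | cRORA | cRORA |
| Discontinuous | <250 µm | <250 µm | iRORA | iRORA |
| Discontinuous | <250 µm | ≥250 µm | iRORA | iRORA |
| Discontinuous | ≥250 µm | <250 µm | iRORA | iRORA |
| Discontinuous | ≥250 µm | ≥250 µm | both | cRORA |

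**Count as written.** Neither 3, cRORA only 1, iRORA only 3, both 1; 3 + 1 + 3 + 1 = 8. These are combinations, not lesion frequencies.

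**Count after the fix.** Neither 0, both 0, iRORA 6, cRORA 2. The combinations that meet cRORA number 1 + 1 = 2 before and 2 after, so the OCT criterion that confirms geographic atrophy is the same.

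**Other rows.** All 8 combinations meet the choroidal hypertransmission row, so none is recorded as free of findings. That row does not require photoreceptor degeneration, so it cannot by itself show which lesions should have been iRORA.

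**Size.** Let N be the number of tear-free lesions short of cRORA that have the RPE and photoreceptor changes, c the share of them that are continuous, and d the number of discontinuous lesions that also meet cRORA. The literal rule gives the iRORA label to N(1 − c) + d lesions, against N after the fix. With d = 0, the loss runs from none (c = 0) to all (c = 1). The article gives neither c nor d. At eye level the loss may be smaller, since an eye with a second, patchy lesion is still iRORA-positive.

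**The case against.** The strongest reply is that the gap needs a strictly literal reading. A category called incomplete, next to one called complete, is evidently meant to hold whatever falls short, and graders who know the terms may use it so. The table sits in a condensed article, and finer conventions may be in a grading manual that is not shown. This stands in part: if graders treat every lesion short of cRORA as iRORA, the gap closes. But the article does not say so. The discontinuity requirement is a stated criterion in the table by which images are graded, not a detail left out.

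Three stronger readings are tempting, and the document does not support them.

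- **That the precursor is scored as absent and geographic atrophy appears from nothing.** The lesion is still recorded as choroidal hypertransmission, and possibly as irregular RPE. Only the iRORA grade is missing.
- **That the primary endpoint is affected.** Geographic atrophy needs atrophy on CFP and FAF as well as cRORA, and iRORA plays no part in it or in its event time. A lesion that satisfies both rows still satisfies cRORA as written, so confirmation stands.
- **That a lesion spends years in the gap.** Dividing 250 µm by an assumed growth of 50, 100 or 200 µm a year gives 5, 2.5 or 1.25 years. But those rates are not in the document, and the sum also assumes growth from zero and a signal that is continuous throughout.

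Nor does the article commit to a hazard ratio for iRORA. The candidate list under Statistical methods does not name it, though that list is open-ended and the outcomes section promises relative risks for the biomarkers generally.

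**Conclusion.** The point holds as a defect in a stated grading rule. Among tear-free lesions with photoreceptor degeneration, 3 of 8 combinations are unlabelled and 1 of 8 is labelled twice. The consequence is confined to iRORA: its prevalence, its longitudinal change, and any relative risk or staging that uses it would be under-recorded or inconsistently graded. The primary outcome is unaffected.

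A pull of an iRORA hazard ratio towards 1 would follow only if such a model is fitted and if small continuous lesions progress at least as often as patchy ones; both are assumptions. The size cannot be fixed from the article, because the share of lesions short of cRORA that are continuous is not given. If that share is small, so is the effect. This is a minor improvement, worth making because it is cheap now.

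**What to change.** In Table 3, define iRORA as hypertransmission of either pattern, with the RPE and photoreceptor changes that the row already requires, in a lesion that does not meet both cRORA 250 µm criteria. State separately how a lesion with an RPE tear is recorded. Simply adding a tear exclusion to iRORA would leave such lesions in neither grade, since cRORA already excludes them. With both changes every tear-free lesion of this kind falls into exactly one grade, and the cRORA criteria and the geographic atrophy definition stay as they are.

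The cost is one line in the grading table and a re-read of this item on the few images already graded. At submission 64 of the planned 1,500 participants had been recruited (64/1,500 = 4.3%), so the re-read is small now and grows with each month of grading.

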**Methods:**

This prospective, longitudinal cohort study aims to recruit 1500 participants from community-based cohorts in Singapore, with a follow-up duration of 5 years. Eligible participants are adults aged 55 years or older without severe systemic illness that would preclude participation.

At baseline, demographic data and medical history will be collected, and visual acuity will be assessed. A basic imaging protocol including color fundus photography (CFP), optical coherence tomography (OCT), and OCT angiography (OCTA) will be performed. Blood samples will be collected from consenting participants. Images will be graded for early signs of AMD, defined as the presence of pathological findings on CFP, OCT, or OCTA.

Participants without early signs of AMD will undergo annual follow-up using the basic imaging protocol. Those with any pathological findings at baseline or during follow-up will undergo an enhanced imaging protocol every 6 months, including ultrawide-field fundus photography, fundus autofluorescence (FAF), OCT, and OCTA. All follow-up visits will be conducted at the Singapore Eye Research Institute (SERI).

Multimodal imaging biomarkers will be integrated with clinical, demographic, genetic, and metabolomic data to assess the relative risk of progression and identify potential predictors. The study protocol has been approved by the SingHealth Centralised Institutional Review Board.

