### Data collection, examinations, and imaging

At baseline visit, whether in a community screening event or OCH, after gathering basic demographic data (age, gender, race), a questionnaire regarding medical history will be completed by the study team. The gathered data should include:

Past ocular history (any eye diseases or ocular surgeries),Family history of retinal diseases (with specific focus on AMD),Past medical historyWith the diagnosis date for each medical conditionPast drug history,steroid use (indication, route, dosage/frequency, start and end date),Social historySmoking (pack/year)work schedule (fixed hours or shift hours), working time and frequency,Longest stretch of undisturbed sleep (<4 hours, 4–6 hours, 6–8 hours, > 8 hours)

Presenting distance visual acuity (VA) is measured monocularly using a modified Early Treatment of Diabetic Retinopathy Study (ETDRS) LogMAR-style chart at 4 meters, with the participant wearing their current habitual distance vision correction, if any. Pinhole VA will also be measured for each eye. Results will be documented in LogMAR.

At next step, Basic imaging protocol consisting of color fundus photography (CFP), optical coherence tomography (OCT) and optical coherence tomography angiography (OCTA) all using Topcon 3D OCT-1 (Maestro 2, Topcon Inc., Tokyo, Japan, wavelength 840nm, and speed of 50,000 A-scan per second) according to the settings mentioned in Table 1 would be conducted for both eyes of each participant without pupil dilation. Scans would be repeated in the case of motion artifacts and/or image quality value (IQV) < 30.

**Table 1 pone.0355953.t001:** Detailed settings of imaging in basic protocol.

Modalities	Imaging setting
Colour Fundus Photography (CFP)	Capture one image at 45 degrees, centred on the fovea (macula), with the optic disc clearly visible in the image
Optical Coherence Tomography (OCT)	Perform 3D volume 6x6 mm (resolution of 1024 and over scan count of 4), centred on the fovea (macula)
Optical Coherence Tomography Angiography (OCTA)	Perform en-face OCTA scans with 3x3mm, (scan resolution 320x320 and over scan count of 4), centred on the fovea (macula)

Images from the Basic Protocol will be graded by research fellows within 2 months for early signs of AMD. This is defined by:

Any presence of drusen, blood, atrophy, CNV, or pigment on CFPAny changes in the outer retinal layers on OCTAny flow signal on OCTA suggestive of a CNV

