All subsequent follow-up visits will occur at SERI, and the follow-up plan will be determined based on the baseline visit imaging:

If none of the early signs of AMD are present at baseline, participants will go through the Basic Protocol in the annual follow up visits till the end of the study.

If any of those signs are present at baseline or at any follow up visit, participants will be required to undergo the enhanced imaging protocol (Enhanced Protocol) during the 6 monthly follow up visits at SERI till the end of the 5-year follow-up. The participants’ flow and disposition are summarized in Fig 1.

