**Fig 1 pone.0355953.g001:**
[figure not shown]
Disposition of participants.

At follow up visits, after reviewing the medical history records and measuring height, weight, and blood pressure, distance visual acuity with or without glasses and pinhole will be measured using the LogMAR chart for both eyes of each participant.

The Basic Protocol involves community-level imaging platforms, including CFP, OCT, and OCTA, which would be performed on both eyes of each participant (without pupil dilation) using Topcon 3D OCT-1 (Maestro 2) according to the settings mentioned in Table 1.

For participants who are part of the Enhanced Protocol, the imaging modalities will include Ultra Widefield Fundus Photography, OCT, FAF, and OCTA, and will all be performed according to the setting described in Table 2.

**Table 2 pone.0355953.t002:** Detailed enhanced imaging protocol.

Imaging modality	Imaging protocols (through dilated pupils)
Optical Coherence Tomography (OCT)	Heidelberg Spectralis (Heidelberg engineering, Heidelberg, Germany) Spectral-Domain OCT, wavelength of 870 nm, A-scan speed of 70,000 scans per second, axial resolution: 3.9 µm, transverse tissue resolution: 6 µm Perform cube scan 6x6mm scan, centred on the fovea (macula), 97 horizontal B-scan, 512 A-scans per line, Automatic Real Time (ART) 7–9, and Enhanced Depth Imaging (EDI) mode on.
Optical Coherence Tomography Angiography (OCTA)	Zeiss PlexElite (PlexElite 9000, Carl Zeiss Meditec) Swept-Source OCTA, wavelength of 1050nm, A-scan speed of 100,000 scans per second Perform en-face OCTA scans with 3x3mm and 6x6mm scan, centred on the fovea (macula) DREAM OCT (Vg200, Intalight) Swept-Source OCTA, wavelength of 1070nm, A-scan and speed of 400,000 A-scans per second Perform 29 x 24 mm OCTA scan (1536 x 1280, R2), centred on the fovea (macula)
Fundus Autofluorescence (FAF)	Heidelberg Spectralis OCT Excitation blue light of 488 nm and a barrier filter beginning at 500 nm Capture two images at 30 and 50 degrees (ART > 50), centred on the fovea (macula), with the optic disc clearly visible in the image Optos (Nikon, Tokyo, Japan) Ultrawide Field FAF
Ultrawide Field Fundus Photography	Optos (Nikon, Tokyo, Japan) Capture one shot at 200 degrees of the retina, centred on the fovea (macula) and includes optic disc

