### Statistical methods

Descriptive statistics will be used to summarize baseline demographic, systemic, ocular, and imaging characteristics of the study cohort. Continuous variables will be presented as mean ± standard deviation (SD) for normally distributed data, or median and interquartile range (IQR) for non-normally distributed data. Categorical variables will be summarized using frequencies and percentages. Normality will be assessed using histograms and the Shapiro–Wilk test.

All analyses will primarily be performed at the eye level. As both eyes from a participant may be included, inter-eye correlation will be accounted for using generalized estimating equations (GEE) or mixed-effects models where appropriate.

Because AMD progression will be assessed at scheduled study visits rather than continuously observed, the primary analysis will evaluate progression to late AMD over predefined follow-up intervals using discrete-time survival models. Standard Cox proportional hazards models may be performed as sensitivity analyses. Where appropriate, interval-censored survival models will be explored.

Variables considered for multivariable models may include demographic factors, systemic risk factors, smoking history, and multimodal imaging biomarkers, including drusen characteristics, pigmentary abnormalities, subretinal drusenoid deposits, hyperreflective foci, drusen volume, double-layer signs, OCTA flow abnormalities, and choroidal parameters. Hazard ratios (HR) and 95% confidence intervals (CI) will be reported.

Longitudinal continuous imaging parameters, including drusen volume, retinal thickness, and choroidal thickness, will be analyzed using linear mixed-effects models to account for repeated measurements over time and within-subject correlation. Logistic regression analyses may additionally be performed for binary outcomes such as conversion to late AMD within predefined follow-up intervals.

Where appropriate, exploratory multivariable models integrating these biomarkers may be constructed to investigate risk stratification. All statistical analyses will be performed using R software (R Foundation for Statistical Computing, Vienna, Austria) and/or IBM SPSS Statistics (IBM Corp., Armonk, NY, USA). All statistical tests will be two-sided, and a p-value <0.05 will be considered statistically significant.

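### Late AMD already present at baseline can be counted as progression at the first Enhanced visit, because baseline imaging cannot establish GA and no rule sets such disease aside as prevalent

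*Protocol article*

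**What the plan says.** **Baseline.** Under *Data collection, examinations, and imaging*, the Basic Protocol "would be conducted for both eyes of each participant without pupil dilation". Table 1 lists a 45-degree colour photograph, a 6x6 mm OCT volume and a 3x3 mm OCTA. FAF is not among them.

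**Follow-up.** Participants with none of the listed signs have annual visits: "participants will go through the Basic Protocol in the annual follow up visits till the end of the study". If any sign is present at baseline or later, "participants will be required to undergo the enhanced imaging protocol (Enhanced Protocol) during the 6 monthly follow up visits at SERI". The Enhanced column of Table 2 is headed "Imaging protocols (through dilated pupils" and adds FAF, ultrawide-field photography and swept-source OCTA at 6x6 and 29x24 mm.

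**Signs.** Blood, atrophy and CNV on the photograph, and flow suggestive of CNV on OCTA, all count as early signs. Neither *Inclusion criteria* nor *Exclusion criteria* mentions late AMD.

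**Outcome.** In *Grading of retinal imaging and outcomes to be measured*, GA needs atrophy on both colour photography and FAF, confirmed by cRORA on OCT. Event time follows the rule "with event time assigned to the first visit at which GA or MNV is detected". Table 3 grading is for participants in the Enhanced Protocol.

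**Analysis.** *Statistical methods* plans to model "progression to late AMD over predefined follow-up intervals using discrete-time survival models". *Study setting* defines progression as a change from early signs to advanced disease.

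**The concern.** A progression analysis needs a time zero at which everyone in the risk set is known to be free of the outcome. Here the imaging at time zero cannot establish one of the two outcome components and is weaker for the other. The better imaging starts at the next visit, and only in people with signs. Disease that was there all along then appears as an early event.

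Two results are at stake. The progression rate, which is the primary outcome, would include prevalent disease. The predictor models would also be affected. Where the Table 3 biomarkers and the event are first read from the same images, a cross-sectional association would be reported as prediction. OCTA flow abnormality shows this most clearly: it is a listed candidate predictor, and abnormal flow is also how the article recognises non-exudative neovascular disease.

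**Working it through.** **Step 1. Follow one case through the stated rules.** Take an eye with GA on the day of recruitment.

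1. The entry criteria do not exclude it.
2. Atrophy on the photograph is graded as an early sign, so the participant goes to the Enhanced Protocol.
3. GA cannot be declared at baseline, because the definition needs FAF and no Basic visit captures it.
4. FAF is first taken at the first 6-monthly visit. GA then meets its definition and is dated there.
5. The article gives no rule that reclassifies it as prevalent.

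This needs no assumption about sensitivity. For MNV the path is the same, but it depends on the lesion being missed on undilated 3x3 mm OCTA.

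**Step 2. Size of the effect on the rate.** There is no plan figure to reproduce, since *Sample size* rests on feasibility. The inputs from the article are N = 1,500 and an incidence of 0.51% (age 40 or older, period not stated). The missed fraction is an assumption.

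- Expected events = 1,500 x 0.0051 = 7.65
- False events = 1,500 x missed fraction
- Inflation = false events / expected events

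| Missed late AMD (assumed) | False events | Inflation on 7.65 | Inflation on 30.6 (4 x 0.51%) |
|---|---|---|---|
| 0.05% | 0.75 | +10% | +2% |
| 0.1% | 1.5 | +20% | +5% |
| 0.2% | 3.0 | +39% | +10% |
| 0.5% | 7.5 | +98% | +25% |

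The last column is shown because *Sample size* expects a rate above 0.51% at age 55 or older. Counts are of participants, whereas the planned analysis is mainly by eye.

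**Step 3. Effect on a sign versus no-sign contrast.** Suppose there is no true difference and all *m* missed cases surface in the fraction *f* with signs. The apparent rate ratio is [(7.65f + m)/f] / [7.65(1 - f)/(1 - f)] = 1 + m/(7.65f).

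| f (assumed) | m = 1.5 | m = 3 | m = 7.5 |
|---|---|---|---|
| 0.3 | 1.65 | 2.31 | 4.27 |
| 0.5 | 1.39 | 1.78 | 2.96 |
| 0.7 | 1.28 | 1.56 | 2.40 |

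**Step 4. Unequal detection of truly new disease.** Assume a constant hazard, 0.51% read as a 5-year risk, and independent misses. A lesion with *n* visits remaining after onset is found with probability 1 - (1 - s)^n, where *s* is the sensitivity per visit. With s = 0.95 at 6-monthly Enhanced visits, the detected risk is 0.00507. For annual Basic visits with s = 0.95, 0.8, 0.6 or 0.4, it is 0.00505, 0.00485, 0.00443 or 0.00369. The ratios are 1.01, 1.05, 1.15 and 1.37. This component is small unless Basic sensitivity is low.

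**The case against.** **The article intends incident disease.** It speaks of MNV developing and of follow-up, and time origin and covariate timing are often left to an analysis plan that is not shown. The intent is clear. However, the outcome definition and the dating rule are stated, and together they give the wrong answer for prevalent GA, so this is more than missing detail. *Strengths and limitations* mentions the undilated baseline only as a matter of photograph gradability.

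**The main biomarker comparisons share one schedule.** This stands. Table 3 features are graded among Enhanced participants, who form the natural risk set under the article's own definition of progression. A reader might infer that every biomarker hazard ratio is distorted by unequal detection, but the documents do not support that. The time-zero problem does remain within this group.

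**A visit-based model would treat 6 and 12 months as equal.** A reader might infer a hazard ratio near 0.5 for the 6-monthly group. *Statistical methods* refers to predefined intervals, not visits, and says interval-censored models will be explored, so this does not follow.

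**OCTA area.** The 29x24 mm scan covers 696 mm² against 9 mm², about 77 times. That says little about finding macular lesions. The Basic OCT volume is 6x6 mm, as in the Enhanced Protocol.

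**Sign-free participants are not lost.** Any later sign moves them to Enhanced imaging, so detection there is mostly delayed.

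**Discrete-time or interval-censored models already handle visit timing.** They handle onset between visits. They do not deal with disease present before the first interval.

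**Conclusion.** The point holds in this form: as the rules stand, GA present at baseline is counted as progression at the first Enhanced visit, and MNV missed at baseline may be. It affects participants with signs only, and the event shares its images with the first grading of the Table 3 predictors.

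The direction is certain for GA, but the size is not known. Under assumed missed fractions of 0.05% to 0.5%, the event count rises by 10% to 98% at 0.51% incidence, or by 2% to 25% at four times that. A reader might infer that about half of all events would be false. That needs the top of the assumed range together with an incidence whose period is not given and which the article expects to be exceeded. Even so, *Strengths and limitations* concedes that progressors may be few, so a handful of misdated events could matter.

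**What to change.** 1. **Signs at baseline.** Make the first Enhanced visit time zero. Classify late AMD found at baseline or at that visit as prevalent, and exclude those eyes from the risk set for both the progression rate and the predictor models. Take Table 3 predictors from that visit and count events from the next.
2. **Sign-free at baseline, switching later.** Keep late AMD found at the switch as an event, interval-censored between the last clear Basic visit and detection. Dropping it as prevalent would discard true conversions. Do not use Enhanced biomarkers from the same visit as its predictors.
3. **Sign versus no-sign contrasts.** Report them as detection-dependent. Add a sensitivity analysis on annual visits using only modalities common to both protocols. It will need a GA criterion that does not use FAF, and it equalises modality but not device or dilation.

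**Cost.** The change is to analysis wording, and *Timeline of the study* reports only 64 participants recruited at submission. Eyes with signs at baseline lose about 6 months of person-time. Some true events in those 6 months are lost too, because they cannot be told apart from disease missed at baseline.
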